### Community Program Feasibility

The feasibility of the program as a community intervention will also be evaluated using a number of metrics including recruitment (achievement of target sample size), attendance (at program sessions), retention (retention rates at 6-month follow-up) and participant perceptions collected from fathers about program satisfaction via a questionnaire (end of program evaluation) that focuses on: open ended feedback of positives and negatives of the program; multiple choice questions regarding prior weight-loss experiences and reasons for joining the program; and Likert scale (5-point) questions anchored from (1) strongly disagree to (5) strongly agree regarding perceptions of program content, program structure, quality of facilitators, quality of program resources, and perceived changes made during the program. Additional information regarding the long term feasibility of the program will be obtained using a semi-structured post program phone interview and a long term process evaluation questionnaire (12 month post program evaluation).

### Sustainability planning

The project is based on the principles of community consultation and will actively seek the ideas and opinions of the communities in which the project will run, including via community forums and leadership from a community advisory panel. Community advisory panel members will represent a broad range of areas including education, local government, health, sports groups and service clubs. The communities will be consulted on the best approaches to engage and recruit participants and run the program in a sustainable manner. The community consultations will also help to identify key local individuals and organizations that can potentially assist in embedding the HDHK program in the local community. The consultations will also assist in identifying suitable local venues for the HDHK program and gaining information about local conditions which may impact on the delivery of the HDHK program (e.g. timing of delivery). Additionally, in order to draw on the strengths and resources of each community and to promote capacity building for sustainability of the program, appropriately qualified community members will be invited to train as facilitators who will conduct the program in their communities. Community consultation meetings will be held in each LGA prior to commencing the program. This will facilitate collaborative partnerships between the researchers and community, and contribute to the sustainability of the program within each community. Any interested community member will be able to attend.

Stage 1 focuses on developing training and implementation manuals that will provide step-by-step instructions on how to run the program. These resources will allow the community to continue to run the program indefinitely after the three year program has been completed. This, along with the training and implementation resources, will provide the basis for gaining support for investment in these strategies by other interested communities, and more importantly governments and health care policy makers. We have also developed a HDHK website http://www.healthydadshealthykids.com.au which provides information for potential participants and other interested parties.

### Data Analysis

Analyses will be performed using PASW Statistics 19 (SPSS Inc. Chicago, IL). Data will be presented as mean (SD) for continuous variables and counts (percentages) for categorical variables. Characteristics of completers versus dropouts will be tested using independent *t *tests for continuous variables and chi-squared (χ^2^) tests for categorical variables. The significance level will be set at 0.05 for all analyses. Analyses will be performed separately for fathers and children and included all randomized participants. Generalized linear mixed models (GLM) will be fitted with an unstructured covariance structure for all primary and secondary outcomes. Differences between means and 95% confidence intervals (CIs) will be determined using GLM.

GLM will be used to assess all outcomes for the impact of group (Intervention and control), time (treated as categorical with levels baseline, 3-months and 6-months) and the group-by-time interaction, these three terms forming the base model. Baseline scores for subjects who dropped out at 3-months and/or 6-months will be retained consistent with an intention-to-treat (ITT) analysis. Mixed models are more robust to the biases of missing data, and provide better control of Type 1 and Type 2 errors than last observation carried forward (LOCF) in Analysis of Variance [70]. Similarly, imputation methods such as LOCF or baseline carried forward may bias results towards the null in obesity trials where untreated overweight men are likely to increase their weight. Age, SES and sex of the child will be examined as covariates to determine if they contributed significantly to the models. If a covariate is significant, two-way interactions with time and treatment will also be examined and all significant terms will be added to the final model to adjust the results for these effects. Effect sizes will be determined using Cohen's *d *[71] and calculated using mean differences and the pooled standard deviation of the group (*d *= M_1 _- M_2_/σ_pooled_). We will also examine a range of secondary outcomes to support the primary outcome (e.g. reduction in waist circumference, increase in physical activity, reduction in kilojoule intake). Additional exploratory models will be fitted to examine if the fathers who have the greatest reduction in weight are also those who have the greatest improvements in the secondary outcomes.

For the community trial, the mean change between pre and post-intervention outcomes will be analyzed using paired Student's t-test when change data are normally distributed. Wilcoxon matched pairs signed rank tests will be used for non-parametric tests. Per protocol analyses for both the RCT and the community trial will be performed for those who attended at least 70% of HDHK sessions and the follow-up assessment visits.

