**Methods/Design:**

The Healthy Dads, Healthy Kids community trial consists of three stages: (i) *Stage 1 - program refinement and resource development *(ii) *Stage 2 - community randomized controlled trial *(iii) *Stage 3 - community effectiveness trial*. The program will be evaluated in five Local Government Areas in the Hunter Valley Region of NSW, Australia. For the community randomized controlled trial, 50 overweight/obese men (aged 18-65 years) from one Local Government Area with a child aged between 5-12 years of age will be recruited. Families will be randomized to either the program or a 6-month wait-list control group. Fathers and their children will be assessed at baseline, post-intervention (3-months) and 6-months. Inclusion criteria are: body mass index 25-40 kg/m^2^; no participation in other weight loss programs during the study; pass a health-screening questionnaire; and access to a computer with Internet facilities. In the community trial, the program will be evaluated using a non-randomized, prospective design in five Local Government Areas. The exclusion criteria is body mass index < 25 kg/m^2 ^or lack of doctor's approval. Measures will be collected at baseline, 3-, 6- and 12-months. The program involves fathers attending seven face-to-face group sessions (three with children) over 3-months. *Measures*: The primary outcome is fathers' weight. Secondary outcomes for both fathers and children include: waist circumference, blood pressure, resting heart rate, physical activity, sedentary behaviors and dietary intake. Father-only measures include portion size, alcohol consumption, parenting for physical activity and nutrition and parental engagement. Process evaluation will determine the fidelity, dose (delivered and received), reach, recruitment and context of the program.

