#### Participants

Overweight or obese (BMI between 25 and 40 kg/m^2^) fathers (aged 18-65 years) with a child aged between 5 and 12 years of age (i.e. primary school age) will be recruited from the local communities using the following strategies: local media releases (print, TV and radio), school newsletters items, school-based presentations, fliers distributed through community notice boards and local businesses, paid advertisements in local newspapers, local networks of sports clubs, service clubs, local government, and community health facilities. Fathers will be screened for eligibility via telephone. Ethics approval has been obtained from the University of Newcastle Human Research Ethics Committee. Written informed consent will be obtained from the fathers prior to their participation as well as child assent.

Fifty fathers will be recruited from one LGA (Maitland) and randomized to either the HDHK program or a 6-month wait-list control group. Fathers (and their children) will be stratified by BMI category (overweight [25-29.9 kg/m^2^], obese class 1 [30-34.9 kg/m^2^], obese class 2 [35-40 kg/m^2^]) and randomized using a computer-based random number-producing algorithm, to intervention or control group. To ensure concealment, the sequence will be generated by a statistician and given to the project manager. Randomization will be completed by a research assistant not involved in assessments and the allocation sequence will be concealed when enrolling participants. Fathers and their children will be assessed at baseline, post-intervention (3-months) and 6-months (3-months post-intervention).

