### Measures

A variety of data collection methods will be used to assess program impact, implementation, participation and fidelity. For the community RCT, participants will be blinded to group allocation at baseline assessment. Baseline assessments will be made 1-2 weeks before program commencement. Assessors will be trained by the same experienced researcher, and for anthropometric measurements, the protocols used are those prescribed by the International Society for the Advancement of Kinanthropometry [29]. A summary and brief description of the measures used for both the RCT and community trial programs is described in Table 3 with more specific details provided below.

**Table 3 T3:** Overview of HDHK RCT and community trial measures

Measure	RCT	Community trial
PHYSICAL MEASURES		
Weight	**Father & child(ren)**: Digital scale	**Father & child(ren)**: Digital scale
Height	**Father & child(ren)**: Portable stadiometer	**Father & child(ren)**: Portable stadiometer
BMI	**Father: **(kg/m^2^). **Child(ren): **(kg/m^2^) and z-scores.	**Father: **(kg/m^2^). **Child(ren): **(kg/m^2^) and z-scores.
Waist circumference	**Father**: 1) level with the umbilicus and 2) the widest point. **Child(ren)**: 1) level with the umbilicus and 2) the narrowest point + z-scores.	**Father**: 1) level with the umbilicus and 2) the greatest circumference point. **Child(ren)**: 1) level with the umbilicus and 2) the narrowest point + z-scores.
Blood Pressure and Resting Heart Rate	**Father & child(ren)**: Digital electronic monitor.	Not measured

PHYSICAL ACTIVITY AND SEDENTARY BEHAVIOR		
Physical activity (PA)	**Father & child(ren)**: Yamax200 pedometers for 7 consecutive days.	**Father**: Modified version of the Godin Leisure-Time Exercise Questionnaire (GLTEQ) [39]. **Eldest child **(Father proxy): Children's Leisure Activities Study Survey (CLASS) questionnaire [41].
Sedentary Behaviors	**Father**: Modified Sitting Questionnaire [42,43]. **Eldest child**: (Mother proxy) modified (CLASS) [41]	**Father**: Modified Sitting Questionnaire [42,43]. **Eldest child **(Father proxy): Indoor based activities section of CLASS [41].

NUTRITION AND DIETARY BEHAVIORS		
Dietary intake	**Father**: Australian Eating Survey (AES) [44]. **Eldest child **(Mother proxy): Australian Child and Adolescent Eating Survey (ACAES) [46].	**Father**: Modified AES relating to 8 key nutritional messages **Eldest child **(Father proxy): Modified AES relating to 8 key nutritional messages.

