##### Sedentary behavior

For the eldest child in the RCT, the mother will complete a modified version of the CLASS, which has been validated in children 5 - 6 and 10 - 12 year of age [41]. In the community trial, fathers will complete a version of the CLASS to obtain a measure of time spent in various sedentary behaviors. Only questions relating to indoor leisure activities will be used (small screen recreation, homework, talking, reading, music and craft activities). To assess their sitting time, fathers will complete an adaptation of the Sitting Questionnaire, which has been shown to be both a valid and reliable measure of sitting time in various domains [42,43].

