##### Dietary intake (Eldest child)

For the eldest participating child in the RCT, their mothers will complete the Australian Child and Adolescent Eating Survey (ACAES), developed and validated for use with Australian children, aged 10 to 16 years [46] and previously shown to be sensitive to changes up to two years [47]. ACAES has also been validated for younger children aged 5-9 years for parent-reported fruit and vegetable intake using plasma carotenoid concentrations [48]. Children's dietary intake will be adjusted relative to body weight and reported as kJ/kg. At follow-up assessments, participants and mothers will be instructed to report on the previous 3-month dietary intake. Dietary intake for the eldest child in community trials will be assessed using a modified version of the ACAES, as described previously, and completed by the fathers.

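### Child outcomes measured on every sibling are analysed with no allowance for family, so their confidence intervals are too narrow when families enter more than one child

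*Protocol article*

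**What the plan says.** **Allocation.** The Abstract states: "Families will be randomized to either the program or a 6-month wait-list control group". The Participants section agrees: "Fathers (and their children) will be stratified by BMI category". Children therefore carry their father's allocation.

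**Who is measured.** Table 3 separates two kinds of child outcome.
- Physical measures are taken on all participating children, for example "Father & child(ren): Digital scale" and, in the RCT, "Father & child(ren): Yamax200 pedometers for 7 consecutive days". Height, BMI with z-score and waist are treated the same way in both stages, as are blood pressure and resting heart rate in the RCT.
- Questionnaire outcomes cover one child per family: "For the eldest participating child in the RCT, their mothers will complete the Australian Child and Adolescent Eating Survey (ACAES"), and "For the eldest child in the RCT, the mother will complete a modified version of the CLASS".

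**How it is analysed.** In Data Analysis, children are modelled separately from fathers: "Analyses will be performed separately for fathers and children and included all randomized participants". A mixed model with unstructured covariance is used for every outcome. Its effects are group, time (baseline, 3 and 6 months) and their interaction, "these three terms forming the base model". The candidate additions are age, SES, sex of the child and their two-way interactions. For Stage 3, pre-post change is tested with a paired t-test or a Wilcoxon signed rank test. No family term or clustering adjustment is mentioned for either stage.

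**The concern.** Siblings share a father, a household and, in the RCT, an allocation. Their changes in weight, waist or daily steps are likely to be positively correlated. A model that links only the visits of one child counts two siblings as two independent pieces of evidence. Standard errors are then too small, intervals too narrow and p-values too low.

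The limit to one child is applied to the questionnaires but not to the physical measures, and a reference to the eldest participating child makes sense only if a family can enter several. Sibling data are therefore expected by design. Influencing children's health behaviours is a stated program aim, and the results are meant to inform wider delivery, so overstated precision on child steps or BMI z-score would matter.

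**Working it through.** **Figure to reproduce.** None. The only sample-size figure, 20 fathers per group at 6 months (50 recruited, 40 / 0.8 = 50), concerns fathers' weight. No child sample size, sibling correlation or design effect is given.

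**Inputs.** From the document: 20 families per arm at 6 months and a two-sided 0.05 level. Assumed: the number of children per family, m, and the sibling correlation in change, ICC.

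**Formulae.** For variable family size, the design effect is DE = 1 + (E[m²]/E[m] − 1) × ICC. The correct interval is wider by the factor √DE. The actual error of a naive two-sided 0.05 test is 2 × (1 − Φ(1.96/√DE)).

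**Worked case.** With 50/40/10% of families entering 1/2/3 children:
- E[m] = 0.5 + 0.8 + 0.3 = 1.6
- E[m²] = 0.5 + 1.6 + 0.9 = 3.0
- E[m²]/E[m] − 1 = 0.875
- At ICC 0.3, DE = 1 + 0.875 × 0.3 = 1.26, √DE = 1.12, and the actual error is 0.081.

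| Families with 1/2/3 children | Mean m | ICC | DE | Interval wider by | Actual error |
|---|---|---|---|---|---|
| All one child | 1.0 | any | 1.00 | 0% | 0.050 |
| 70/25/5% | 1.35 | 0.1 | 1.06 | 3% | 0.057 |
| 70/25/5% | 1.35 | 0.3 | 1.18 | 9% | 0.071 |
| 70/25/5% | 1.35 | 0.5 | 1.30 | 14% | 0.085 |
| 50/40/10% | 1.6 | 0.1 | 1.09 | 4% | 0.060 |
| 50/40/10% | 1.6 | 0.3 | 1.26 | 12% | 0.081 |
| 50/40/10% | 1.6 | 0.5 | 1.44 | 20% | 0.102 |
| 30/50/20% | 1.9 | 0.1 | 1.12 | 6% | 0.064 |
| 30/50/20% | 1.9 | 0.3 | 1.35 | 16% | 0.091 |
| 30/50/20% | 1.9 | 0.5 | 1.58 | 26% | 0.119 |

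**Simulation check.** This used 20 families per arm, a 40/45/15% mix (mean 0.40 + 0.90 + 0.45 = 1.75), no treatment effect and a naive two-sample t-test on children, with 10,000 trials. Rejection was 6.4%, 7.5%, 8.9%, 9.9% and 10.7% at ICC 0.1, 0.2, 0.3, 0.4 and 0.5. The formula gives 6.2%, 7.4%, 8.7%, 9.9% and 11.1%. A test on family means in the same simulation held 4.6% to 5.3%. With the 70/25/5% mix, simulation gave 5.6% to 8.5% over ICC 0.1 to 0.5.

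**Would a family random intercept repair it?** A family intercept with variance τ² gives any two siblings covariance τ² at every pair of visits. For change between two visits, the implied sibling covariance is τ² − τ² − τ² + τ² = 0. The treatment effect is the group-by-time contrast, which is about change, so the intercept largely cancels from it. A check with a family intercept plus an unstructured within-child covariance left the error at 7.4%, 8.7% and 11.1% for ICC in change of 0.2, 0.3 and 0.5. Those are the naive values.

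**Stage 3.** The variance of a mean change across children is multiplied by the same DE, so the width factors also apply to the paired t-test. No separate figure was computed for the Wilcoxon test.

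**The case against.** The strongest reply is that this is a condensed article. The three base-model terms are fixed effects, as are the candidate covariates. The article never says which unit defines the covariance, and it does not exclude a family level. A full protocol or analysis plan could contain one. This stands in part: a reader might infer that the authors declare siblings independent, and the text does not say so. But the article does fix the covariance structure, the model terms, the covariate rule and, for Stage 3, named tests that assume independent pairs. Followed as written, with time as the only repeated dimension mentioned, that specification does not fit the stated allocation and measurement of children. If an unseen plan already handles family, one sentence settles the matter.

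Three further points stand.
- Eligibility requires only one child aged 5 to 12, so the effect could be small or nil.
- The affected outcomes are secondary, and Data Analysis describes secondary outcomes as supporting the primary one.
- Stage 3 is not randomised, so an argument from the unit of randomisation does not carry over to it. The fault there is only that the paired tests assume independent children.

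**Conclusion.** The point holds for secondary outcomes measured on every participating child: weight, BMI and z-score, and waist in both stages, plus blood pressure, heart rate and pedometer steps in the RCT. When families enter more than one child and siblings' changes are positively correlated, the stated analyses give intervals that are too narrow.

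The size rests wholly on assumptions, because the document supplies neither family size nor a sibling correlation. Over the assumed range the distortion runs from slight to an error rate a little over twice nominal, and the upper end needs both many multi-child families and a correlation of 0.5.

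A reader might infer that the trial's main result is compromised, or that all child findings are. The documents support neither reading. The primary outcome has one father per family, and diet, sedentary behaviour, questionnaire activity and parenting measures refer to the eldest child only.

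**What to change.** **RCT, all-children outcomes.** Use family-clustered (robust) standard errors, or a family-by-time random effect, meaning a family-level covariance across visits with children nested in family. Base the degrees of freedom on the number of families; at 20 per arm a two-group family-level comparison has 20 + 20 − 2 = 38. State that a family random intercept alone is not relied on.

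**Stage 3, all-children outcomes.** Analyse child change with family-clustered errors, or average siblings and apply the planned test to family means.

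**Unchanged.** The models for fathers' outcomes and for eldest-child-only outcomes can stay as they are.

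**Cost.** Somewhat wider intervals for the affected child outcomes and a little more analysis work. No new data, visits or participants are needed, provided the dataset identifies which children belong to which father.

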#### Sample size

For the RCT, based on 80% power to detect a significant weight loss difference between groups of 3 kg, assuming SD = 5 (*P *= 0.05, two-sided) a sample size of 20 fathers for each group will be needed at 6 months. Assuming a 20% attrition rate [14], a total sample of 50 fathers will be required. Participants will be blind to group allocation at baseline assessment. Once baseline assessments are completed, participants will receive a sealed envelope with a note advising their group allocation. The wait-list control group will receive no information or intervention before attending the 3- and 6-month follow-up assessment sessions. There will be a 6-month wait-list control group as (a) ethically every overweight man is deserving of an intervention and is unlikely to remain weight stable; (b) randomization to 'no' intervention for a greater length of time is unlikely to be acceptable and is likely to lead to high attrition compromising study integrity.

Stage 3 - Community effectiveness trial design

When translating evidence-based programs into real-world settings, ongoing modifications are required based on the unique characteristics of the settings and populations. Modifications will be made to the program based on both outcome and process evaluation from the community RCT and each subsequent program implementation in 2011 and these will be documented. The goal will be to develop a comprehensive model of a real-world intervention for application in communities through updating materials, developing standardized train-the-trainer education and resources and ongoing evaluation of the implementation of the intervention with a final evaluation conducted in 2012.

The HDHK program will be evaluated for effectiveness in the community roll-out using a non-randomized, prospective design. This evaluation will be conducted in both 2011 and 2012 in the five local government areas. The exclusion criteria is minimal to align with a true translational model and will only include BMI < 25 or lack of doctor's approval. Measures (detailed below) will be collected at baseline, post-intervention, and 6 and 12 months post-baseline. We aim to recruit 15-20 fathers from each area. Results from each program will be pooled and it is expected at least 200 families will participate in the community trial of the HDHK program.

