#### Primary outcome measure

The primary outcome measure is body weight of the fathers at 6-month follow-up. Weight will be measured with fathers wearing light clothing, without shoes on a digital scale to 0.1 kg (model CH-150 kp, A&D Mercury Pty Ltd, Australia). Weight will be recorded twice and the average of the two measures reported. The same protocol will be followed to record children's weight.

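### The RCT base model leaves the randomised arms' baseline means free, so it compares change without conditioning on baseline: unbiased, but less precise than a common-baseline model, mainly for secondary outcomes

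*Protocol article*

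**What the plan says.** All points are from the protocol article.

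- **Data Analysis, model.** Besides group, the terms are "time (treated as categorical with levels baseline, 3-months and 6-months) and the group-by-time interaction, these three terms forming the base model". Baseline is thus a level of the response. The models "will be fitted with an unstructured covariance structure for all primary and secondary outcomes".
- **Data Analysis, covariates.** "Age, SES and sex of the child will be examined as covariates to determine if they contributed significantly to the models". An outcome's own baseline value is not on this list.
- **Data Analysis, dropouts.** "Baseline scores for subjects who dropped out at 3-months and/or 6-months will be retained consistent with an intention-to-treat (ITT) analysis".
- **Primary outcome measure.** "The primary outcome measure is body weight of the fathers at 6-month follow-up".
- **Sample size.** The RCT is planned on "80% power to detect a significant weight loss difference between groups of 3 kg, assuming SD = 5", with 20 fathers per group at 6 months and 50 in total after 20% attrition. Fathers learn their allocation only after the baseline assessment.
- **Participants.** Randomisation is stratified by three BMI categories.

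**The concern.** Baseline values are collected before fathers know their arm, and the arms are formed by randomisation, so the expected baseline means are equal. The stated model does not use this. It estimates six free means (two arms at three times), and its 6-month interaction subtracts each arm's observed baseline mean in full. When baseline and follow-up correlate only moderately, full subtraction over-corrects a chance baseline difference and adds noise. A model that conditions on baseline removes only the part that baseline predicts.

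Precision is scarce, with about 40 completers planned. The same base model is fixed for all RCT outcomes, so any loss is repeated across them. It is largest where tracking is weakest, and those are the behavioural and parenting outcomes on which the article's claims about lifestyle and children depend.

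**Working it through.** **1. The plan's own figure.** Inputs from Sample size: difference 3 kg, SD 5, two-sided 0.05, power 80%.

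- n per arm = 2 × 5² × (1.960 + 0.842)² / 3² = 43.6, so 44 (45 with the t distribution). The stated 20 is not reproduced.
- At 20 per arm the standard error is 5 × √(2/20) = 1.58 kg. Power is Φ(3/1.58 − 1.96) = 47.5%, or 46% with the t distribution.
- The step from 40 to 50 does reproduce: 40 / (1 − 0.20) = 50.

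**2. What the stated model estimates.** With complete data, the 6-month group-by-time term equals the difference between arms in mean change from baseline. Let σ be the SD at one visit (the same at both visits), ρ the correlation between baseline and 6 months, and n the number per arm.

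- Change contrast: variance = (2/n) × 2σ²(1 − ρ)
- Baseline-adjusted contrast: variance = (2/n) × σ²(1 − ρ²)
- Ratio, adjusted to change = (1 + ρ)/2, a cut of (1 − ρ)/2

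**3. Size of the loss.** The article states no ρ, so a range is shown. Columns 3 and 4 are separate allowances, not cumulative. Column 3 multiplies the ratio by 1 + 1/36, the cost of estimating the slope with 40 completers. Column 4 compares the free-baseline and common-baseline models at 25 per arm with 20% lost by 6 months, assuming equal correlations between visits and a known covariance.

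| Assumed ρ | Cut, (1 − ρ)/2 | Cut after slope cost | Cut with 20% dropout |
|---|---|---|---|
| 0.5 | 25% | 23% | 21% |
| 0.7 | 15% | 13% | 13% |
| 0.9 | 5% | 2% | 4% |

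A simulation of the two models (25 per arm, 20% with baseline only, known covariance) gave cuts of 18%, 14% and 4% at ρ = 0.5, 0.7 and 0.93.

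In terms of completers, using the ratios after slope cost, 20 fathers per arm would be worth 20/0.771 = 25.9 at ρ 0.5, 20/0.874 = 22.9 at ρ 0.7 and 20/0.976 = 20.5 at ρ 0.9.

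**4. Fathers' weight.** Assume that SD 5 is the SD of change and that weight has a between-father SD of 10 to 16 kg. The article states neither. Then ρ = 1 − 25/(2 × SD²):

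- SD 10: 1 − 25/200 = 0.875, ratio 0.938
- SD 12: 1 − 25/288 = 0.913, ratio 0.957
- SD 16: 1 − 25/512 = 0.951, ratio 0.976

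The cut is 2% to 6% before the slope cost and about 0% to 4% after it. In a simulation at ρ 0.93 with 20 per arm, the standard errors were 1.577 kg (change) and 1.571 kg (adjusted), and power was 45.3% and 45.4%.

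**The case against.** The strongest reply is that nothing here is an error. Baseline is in the model as a response level, the interaction subtracts it, and the contrast is standard and unbiased under randomisation. That stands. A reader might infer from the covariate list that baseline is ignored altogether, and the documents do not support that.

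The primary outcome is also barely affected, as step 4 shows. Stratification by BMI category further limits chance imbalance in fathers' weight, though it does little for outcomes only weakly related to BMI. Both points stand.

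A reader might also infer that the primary comparison is of raw 6-month weights, because the primary outcome is worded as weight at that visit and Data Analysis speaks only of differences between means. That comparison would be far less precise. The article does not say that it will be used. The sample size is framed as a difference in weight loss, and the model is built on group-by-time, so both point to change. The contrast is unnamed, but that does not show the wrong one was chosen.

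Finally, the case for secondary outcomes rests on assumed correlations, and the simple (1 − ρ)/2 figures leave out dropout and slope estimation. This is fair, and for that reason a range and the reduced figures are given. At moderate ρ the gain shrinks but remains.

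**Conclusion.** The point holds as a free gain in efficiency, not as a flaw in validity. The stated model compares change with free baseline means, and a common baseline mean would be more precise. The size depends on ρ, which the article does not give: a variance cut of about 18-23% at 0.5, 13-14% at 0.7 and 2-4% at 0.9. It is negligible for fathers' weight (0 to about 2 power points at the implied ρ of 0.88 to 0.95). It is material mainly for secondary outcomes with moderate tracking, such as steps, sitting time, diet, blood pressure and parenting scores. That these outcomes track moderately is an assumption.

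A reader might hope that the change would rescue the sample size. It would not: with SD 5 as the SD of change, the requirement falls only from 44 per arm to 42 at ρ 0.9 or 43 at ρ 0.95. The stated 20 per group needs its own correction.

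**What to change.** Keep the mixed model, the unstructured covariance and all randomised participants, but constrain the two arms to one baseline mean. The fixed effects become time (three levels), group-by-3-month and group-by-6-month. The two group terms should be coded as explicit indicators. Deleting the group main effect while leaving a full group-by-time factor in the model only re-expresses the same six free means. Name the 6-month group contrast from this model as the primary estimate, and use the same form for every RCT outcome measured at baseline.

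Entering baseline as a covariate for the 3- and 6-month values is not an equal substitute. It loses fathers who have only a baseline value, against the plan's commitment to include all randomised participants and keep dropouts' baseline scores.

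The cost is one sentence in Data Analysis and a changed model statement, with no new data and no more participants. The only added assumption is equal expected baseline means, which randomisation supplies.
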